### Exclusion criteria

The exclusion criteria included any history of neuromuscular and cardiorespiratory disease (self-declared) and any contraindications of aquatic physiotherapy: hydrophobia, cutaneous wounds, and infectious diseases [20]. Volunteers may not have participated in another physical training program for at least two months from the beginning of the data collection and may not participate in another training or nutritional monitoring program during the aquatic intervention. For those who use anti-hypertensive drugs and hormone replacement therapy, a change in medication class or dose will not be allowed. As a criterion of adherence after the training period, data from samples that did not obtain at least 80% frequency in the sessions will be excluded.

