### Randomization and allocation

Randomization will be performed after baseline assessments. Sequentially numbered opaque sealed envelopes will be prepared ahead of time and randomly assigned by a computer-generated table of random numbers in a 1:1 proportion. A person blinded to the study protocol will perform the randomization and provide the group assignment to the treating physical therapist. Volunteers will be allocated to the water group, which will be submitted to the 12-week DWR-IT program, or to the control group, which will not be submitted to intervention and will be instructed not to engage in any kind of structured physical exercise training and to keep the life activities identified at baseline. The International Physical Activity Questionnaire (IPAQ) will be applied before and after the intervention in order to assess the level of physical activity. Failure to follow the recommendations is an exclusion criterion in the study (Fig. 2).

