#### Control group

The control group will not undergo any form of treatment. Volunteers will be instructed not to change their daily usual activities or diet or participate in other physical activities. During intervention, the volunteers will be monitored by phone calls from the researchers every week, and IPAQ and food frequency questionnaire (FFQ) will be used to monitor and control the level of physical activity and the frequency and quantity of food consumed; both will be applied before intervention, at week 6, and after the intervention period. If there are changes in dietary habits or level of physical activity, the volunteers will be excluded from the study.

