#### Sample size

The sample size was performed on the basis of a pilot study, conducted previously with middle-aged women submitted to a DRW protocol [32]. Sample size calculation was performed by using G*Power version 3.1 software (Heinrich-Heine-Universität Düsseldorf, Düsseldorf, Germany). The maximum distance covered in 6MWT assessed before (566.2 ± 51.8 m) and after (625.1 ± 73.6 m) the DWR program was considered the main outcome. Significance level was set at 5% with 80% power. A sample of 12 participants per group was suggested. Given a possible 20% dropout rate, 15 participants will be required per group, thus totaling 30 participants.

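### Fifteen per group leaves exactly 12 after 20% dropout, so nothing is held back for the plan's own post-randomisation exclusions and the stated 80% power is not assured

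*Protocol article*

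**What the plan says.** The Sample size section of the protocol article takes the six-minute walk distance as the main outcome and cites pilot values from a deep water running programme: "The maximum distance covered in 6MWT assessed before (566.2 ± 51.8 m) and after (625.1 ± 73.6 m) the DWR program". It continues: "Significance level was set at 5% with 80% power", then "A sample of 12 participants per group was suggested". The only allowance for loss is "Given a possible 20% dropout rate, 15 participants will be required per group", 30 in total.

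Three other sections remove people or data after randomisation:

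- **Exclusion criteria:** as a criterion of adherence applied after the training period, "data from samples that did not obtain at least 80% frequency in the sessions will be excluded". Only the water group has sessions, so this can affect only that arm.
- **Randomization and allocation:** after the instruction to controls to avoid structured exercise and keep their baseline activities, "Failure to follow the recommendations is an exclusion criterion in the study".
- **Control group:** "If there are changes in dietary habits or level of physical activity, the volunteers will be excluded from the study". No threshold for a change is given. Activity and diet questionnaires are applied before, at week 6 and after, with weekly phone calls.

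The Sample size section mentions none of these rules, and no expected rate is given for any of them.

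**The concern.** The loss allowance and the exclusion rules were not visibly fitted together. A person who withdraws and a person who is measured at week 12 but has attended too few sessions are different kinds of loss. The plan discards both and budgets in words for dropout only. Because the inflation returns exactly to 12, any exclusion beyond a full 20% dropout leaves an arm smaller than the plan says it needs.

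At stake is the 80% power on the main outcome. The rules also act differently in the two arms, so the arms could shrink unequally and for reasons connected with the assigned group.

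**Working it through.** **Inputs.** From the Sample size section: 12 per group, 20% dropout, 15 per group, 5% significance, 80% power, walk distance 566.2 (SD 51.8) m before and 625.1 (SD 73.6) m after. Not given: sidedness (two-sided taken here), the pre-post correlation r, and any exclusion rate. The values used for these are assumptions.

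**1. The plan's own figure.** 12/(1 − 0.20) = 15 per group, 30 in total. This reproduces. In reverse, 15 × 0.80 = 12.0: three dropouts use up the whole allowance, and one further exclusion in that arm leaves 11.

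**2. How much the attendance rule tolerates.** The programme has 36 sessions, and 0.80 × 36 = 28.8, so 29 sessions are needed. A water-group participant who misses 8 has attended 28/36 = 77.8%, and the data are removed even if the week-12 measurement was made.

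**3. Chance that an arm falls below 12.** Treat the number analysable out of 15 as binomial with probability 1 − q, where q is the total loss in that arm.

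| Assumed total loss q | Expected number analysable, 15(1 − q) | Chance of fewer than 12 |
|---|---|---|
| 10% | 13.5 | 5.6% |
| 15% | 12.75 | 18% |
| 20% | 12.0 | 35% |
| 28% (20% dropout, then 10% of the rest excluded: 1 − 0.8 × 0.9) | 10.8 | 64% |
| 36% (20% dropout, then 20% of the rest excluded: 1 − 0.8 × 0.8) | 9.6 | 85% |

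These are per-arm figures. One common exclusion rate should not be read across both arms, because the rules are largely arm-specific.

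**4. What a smaller arm does to power.** The pilot figures are before-and-after values, and 12 is consistent with a two-sided paired t-test for r between about 0.49 and 0.54, so that test is used here. The change is 625.1 − 566.2 = 58.9 m. The SD of the change is √(51.8² + 73.6² − 2r × 51.8 × 73.6). Power is from the noncentral t distribution with n − 1 degrees of freedom and noncentrality (58.9/SD of change) × √n.

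| Assumed r | SD of change (m) | Standardised effect | Power, n = 12 | n = 11 | n = 10 |
|---|---|---|---|---|---|
| 0.50 | 65.5 | 0.90 | 81% | 77% | 72% |
| 0.53 | 63.6 | 0.93 | 83% | 79% | 74% |
| 0.60 | 59.4 | 0.99 | 88% | 84% | 80% |

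The middle row is the case in which the SD of the change equals the pooled SD, √((51.8² + 73.6²)/2) = 63.6 m. From 12 to 10, each participant lost costs roughly 4 to 5 percentage points.

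**The case against.** The strongest objection is that the documents do not show a shortfall. The 20% is described as a possible rate, so it is an allowance and not a forecast that three of 15 will leave. If dropout and exclusions together reach only 10% in an arm, the chance of falling below 12 is 5.6%. Two of the three rules speak of exclusion from the study, so a single loss allowance may have been meant to include those people. All of this stands. A reader might infer that following the plan will take the groups below 12 and that 80% power will be missed. The text does not support that: it gives no exclusion rate, and the shortfall needs total loss above 20% in an arm.

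The power figures also depend on a correlation that the document does not state. At r = 0.60 an arm of 11 still has 84%, and an arm of 10 sits at about 80%. That stands too, which is why a range is shown.

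A reader might also fold in the low between-group power. With 58.9 m and an SD of 63.6 m, a two-sample test has about 58% power at 12 v 12. That is a separate problem with how 12 was derived and should not be used to enlarge this one.

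What the objection does not remove is the lack of margin. The attendance rule discards data after the training period, from people who may well have been measured. That goes beyond dropout in its usual sense, and the Sample size section does not say that it is covered.

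**Conclusion.** The point holds in conditional form. The inflation from 12 to 15 is arithmetically correct and leaves no reserve, while the plan contains three further ways of losing randomised participants that the sample-size text does not mention. If they come on top of 20% dropout, an arm has fewer than 12. The stated 80% power is therefore not assured; it is not shown to be missed.

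If exclusions did come on top of the dropout allowance, a total loss of 28% to 36% (assumed) would make an arm below 12 more likely than not. A drop from 12 to 10 would cost about 8 to 9 percentage points of paired power across r = 0.50 to 0.60. These sizes rest on assumed loss rates, independent losses within an arm, a two-sided paired test and an assumed correlation.

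**What to change.** Make the primary analysis include all randomised participants who have a week-12 measurement, in the group to which they were assigned. Use the attendance, activity-instruction and diet or activity-change rules only to define a per-protocol set for a sensitivity analysis. The 20% allowance then has to cover true loss only, and removal of participants by rules that differ between arms no longer affects the primary comparison.

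If the exclusions are kept in the primary analysis instead, the Sample size section should say whether the 20% includes them. It should also restate the power at the number expected per arm after dropout and exclusions combined, with the assumed rates and correlation shown.

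The cost of the first option is wording in the Exclusion criteria, Randomization and allocation, Control group and Analysis sections. Participants who are excluded must still be measured at week 12. The primary estimate will include non-adherent participants and may be somewhat diluted. No extra recruitment is needed, which matters because the trial is already in data collection. The cost of the second option is a less favourable stated power.

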#### Analysis

The normality and homogeneity of data variance will be verified through the Shapiro–Wilk and Levene tests, respectively. For the variables with normal distribution, the two-way mixed-design analysis of variance (ANOVA) test (a repetition factor and a group factor), followed by Bonferroni post hoc, will be applied. For variables with non-normal distribution, the Wilcoxon tests will be used to compare the differences between times and the Mann–Whitney test to compare differences between groups. In this case, the Bonferroni adjustment will be used *a priori*. In all tests, the significance level of 5% will be considered. The effect size will be calculated by using Cohen’s d, and the results interpreted on the basis of Cohen as follows: small (0.21–0.49), medium (0.50–0.79), or large (≥0.80) [33].

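### Levene's test is planned but its result changes nothing; naming an unequal-variance analysis in advance would be a cheap safeguard, because training may make the water group more variable

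*Protocol article*

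**What the plan says.** The Analysis section announces two checks: "The normality and homogeneity of data variance will be verified through the Shapiro–Wilk and Levene tests, respectively". It then gives two routes. Normal variables go to ANOVA: "the two-way mixed-design analysis of variance (ANOVA) test (a repetition factor and a group factor), followed by Bonferroni post hoc, will be applied". The other route is "For variables with non-normal distribution, the Wilcoxon tests will be used to compare the differences between times and the Mann–Whitney test" for comparing the groups. Both routes are entered on normality. No consequence is attached to Levene's test, and no unequal-variance method is named.

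The Sample size section takes the 6MWT as the main outcome, with pilot values "assessed before (566.2 ± 51.8 m) and after (625.1 ± 73.6 m) the DWR program". It plans 12 per group, raised to 15 for a 20% dropout.

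Two rules can change the numbers analysed. Under Exclusion criteria, "data from samples that did not obtain at least 80% frequency in the sessions will be excluded"; only the water group has sessions to attend. Under Control group, controls whose diet or activity level changes are excluded. Randomization and allocation, where assignment is 1:1, also excludes volunteers who do not follow the recommendations.

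**The concern.** A check that cannot alter the analysis gives no protection. The mixed ANOVA pools the variance of the two arms, and the protocol's own pilot suggests that training spreads out walking distance.

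Pooling can do harm in two ways. The between-arm test becomes too liberal if the smaller analysed arm is the more variable one, and too conservative if the larger arm is. Separately, a within-arm contrast built on the pooled error gives the water group too small a standard error and the controls too large a one, even when the arms are equal in size. The Abstract states its expected benefits as changes in the water group, so the within-water contrast is likely to be quoted.

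**Working it through.** **Inputs from the article.** Pilot SD 51.8 m before and 73.6 m after; planned 12 analysed per arm, and 12/0.8 = 15 randomised per arm, which reproduces the stated inflation. The figure of 12 itself is reproduced by a two-sided paired t test at 5% and 80% power if the pre-post correlation r is 0.5: SD of change 65.5, standardised change 58.9/65.5 = 0.90, n = 12. The article does not state r.

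**Assumptions, not in the article.** Control SD is 51.8 m at both times; r is 0.5 to 0.8; data are normal; there are two time points for the 6MWT.

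**Step 1: pilot variance ratio.** (73.6/51.8)² = 5417/2683 = 2.02.

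**Step 2: variance of change.** With two arms and two times, the ANOVA interaction is the pooled-variance t test on change.
- Water: √(51.8² + 73.6² − 2r × 51.8 × 73.6) = 65.5 at r = 0.5 and 44.7 at r = 0.8.
- Control: 51.8 × √(2(1 − r)) = 51.8 and 32.8.
- Variance ratio, water to control: 1.60 and 1.86.

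**Step 3: true error of the nominal 5% between-arm test.** These come from simulated trials with no effect, at least 100,000 per setting. Ranges cover r = 0.5 to 0.8; repeated runs differ by 0.1 to 0.2 percentage points.

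| Water v control | Pooled | Welch |
|---|---|---|
| 12 v 12 | about 5.1% | about 4.9% |
| 12 v 15 | 5.7–5.9% | about 5.0% |
| 10 v 15 | 6.1–6.6% | about 5.0% |
| 15 v 10 | 3.8–4.1% | about 4.9% |

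The expected pooled standard error divided by the true one is 1.00 at 12 v 12, 0.97 at 12 v 15 and 0.94 to 0.95 at 10 v 15.

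**Step 4: within-arm contrasts at 12 v 12, if the pooled error is used.** The pooled SD of change is √((65.5² + 51.8²)/2) = 59.0 at r = 0.5, and √((44.7² + 32.8²)/2) = 39.2 at r = 0.8.
- Water: 59.0/65.5 = 0.90 and 39.2/44.7 = 0.88, so the standard error is 10–12% too small.
- Control: 59.0/51.8 = 1.14 and 39.2/32.8 = 1.20, so it is 14–20% too large.
- With Bonferroni over the two within-arm contrasts (2.5% each), the water contrast rejects in about 4.1–4.8% of null trials.

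**Step 5: would acting on Levene help?** Hardly. With SDs of 73.6 and 51.8 it rejects in only about 13–18% of trials at 12 per arm and 15–21% at 15 per arm, depending on whether it is centred on the median or the mean.

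**The case against.** The strongest reply is that the planned comparison is sound. Allocation is 1:1, the plan foresees equal loss, and at 12 v 12 the between-arm error rate is right. This stands.

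A reader might infer that the attendance rule makes the arms unequal and that the trial's error bars are therefore wrong. The article does not support that. Controls face exclusions of their own, nothing shows which arm will lose more, and losing more controls makes the test conservative. A 10 v 15 split needs a third of the water group lost and no controls, which no section predicts.

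A reader might also quote 7.5–8.3% as the error rate of the within-water contrast. That figure tests at an uncorrected 5%, whereas the plan prescribes Bonferroni. With two contrasts at 2.5% each, the chance of any false rejection across the pair is about 5.2–5.6% at 12 v 12, close to nominal. The pooled error term is itself an assumption: paired contrasts on each arm's own data would fit the wording and remove this part of the problem.

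The variance evidence is thin. It is a before-after ratio in one trained group of women, of unstated size, for one outcome. If that pilot had 12 to 15 participants (assumed), a test of equal paired variances at r = 0.5 to 0.8 would give p of about 0.05 to 0.22.

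Lastly, a fallback for unequal variances may stand in a full plan that is not shown. That lowers the weight of the point. It does not remove it, because the article states its routing rule and that rule leaves one of the two checks without effect.

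**Conclusion.** The point holds as a modest, conditional one. Levene's test is idle as written, and a normal variable with unequal variances stays with a pooled-variance analysis. For the 6MWT, unequal arm variances are plausible but not established, since they rest on the control SD staying at the pilot baseline value.

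The arm-specific exclusions can make the analysed arms unequal but need not. If they stay equal, the between-arm test is essentially correct. If they do not, its true level lies between about 3.8% and 6.6% over the splits examined, and the direction cannot be known in advance. The within-water standard error is 10–12% too small only if the post hoc tests borrow the pooled error. None of this invalidates the main comparison as planned; it justifies a cheap improvement.

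**What to change.** In the Analysis section, delete Levene's test as a check without consequence and prespecify an analysis that allows unequal variances: a Welch test on the between-arm difference in change, or a model with arm-specific residual variance. State that each within-arm interval uses that arm's own SD of change. Do not make the choice depend on Levene's result, because the test has little power at this size.

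The cost is one or two sentences and a small loss of degrees of freedom. If the variances are in fact equal, power at 12 v 12 is about 80.0% with Welch against 80.3% pooled.

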#### Muscle strength and endurance test

The chair stand test (CST) evaluates inner limb muscle strength and endurance and consists of 30-s sit-to-stand repetition movements in a chair without using the upper limbs [24]. The arm curl test (ACT) evaluates upper limb strength and endurance and consists of performing the greatest number of elbow flexion and extension for 30 s with 2-kg dumbbells for women and 4-kg dumbbells for men [26]. After both tests are performed, the number of repetitions will be recorded.

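### The pre/post mixed ANOVA leaves baseline unadjusted and names no deciding term; a baseline-adjusted ANCOVA would be a cheap improvement, though not a guaranteed gain in power

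*Protocol article*

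**What the plan says.** The Analysis section of the protocol article sets the method for normally distributed variables: "the two-way mixed-design analysis of variance (ANOVA) test (a repetition factor and a group factor), followed by Bonferroni post hoc, will be applied". Variables that are not normal get Wilcoxon tests between times and Mann-Whitney tests between groups. No baseline covariate appears in either branch, and no single term or contrast is named as the test of the intervention.

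On timing, the Randomization and allocation section states "Randomization will be performed after baseline assessments", so every baseline value precedes allocation. Allocation is "randomly assigned by a computer-generated table of random numbers in a 1:1 proportion", with no stratification described.

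The Sample size section takes 6MWT distance, "assessed before (566.2 ± 51.8 m) and after (625.1 ± 73.6 m) the DWR program was considered the main outcome", and then sets the error rates: "Significance level was set at 5% with 80% power". The number that came out of the calculation is reported next: "A sample of 12 participants per group was suggested". An allowance for losses raises it to the final target: "Given a possible 20% dropout rate, 15 participants will be required per group, thus totaling 30 participants".

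A week-6 measurement is stated only for the physical activity and food frequency questionnaires (Control group section). Two 6MWT occasions, before and after, is therefore an inference; the schedule figure is not shown.

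**The concern.** A two-by-two mixed ANOVA returns a group main effect, a time main effect, an interaction and a set of pairwise post hoc tests. Only the interaction addresses the randomised question. The group main effect averages in a value taken before treatment. The time effect and the within-group contrasts can be significant because one arm changed, without any demonstrated difference between arms. With no term named, the choice among them stays open until the results are in.

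Even if the interaction is meant, it subtracts the full baseline value from the outcome, whatever the actual pre-post slope. In arms of 12 to 15 a sizeable chance difference at baseline is likely, and subtraction corrects it exactly only when that slope is 1. The stake is a clearly identified treatment effect in metres, less dependent on baseline luck.

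**Working it through.** **Inputs.** From the Sample size section: SD before 51.8 m, SD after 73.6 m, change 625.1 - 566.2 = 58.9 m, 12 per arm before dropout, alpha 5%, power 80%. Assumed, because not given: two-sided test; pre-post correlation r from 0.3 to 0.9; a between-group effect of 58.9 m; the same SDs in both arms unless stated otherwise.

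**1. The plan's own figure.** SD of change = sqrt(51.8² + 73.6² - 2r × 51.8 × 73.6). At r = 0.5 this is sqrt(8100.2 - 3812.5) = 65.5 m, and 58.9/65.5 = 0.90. A paired t-test at 80% power then needs 12 people, and 12/(1 - 0.2) = 15. The stated figure is thus reproduced as a within-group calculation.

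**2. Equivalence.** With two time points the group-by-time F equals the squared two-sample t on change. On simulated data with 12 per arm both came to 0.12851 on 22 degrees of freedom. This holds for the interaction only.

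**3. Group main effect.** It compares the person-level mean of the two measurements, so the effect halves to 29.45 m. The SD of that mean at r = 0.5 is sqrt(8100.2 + 3812.5)/2 = 54.6 m. Power at 12 per arm is about 24%, against 56% for the interaction.

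**4. Chance imbalance.** Standard error of the baseline difference = 51.8 × sqrt(2/12) = 21.1 m, which is 36% of 58.9 m. Given a baseline difference D, the change score is off by (b - 1) × D, with b = r × 73.6/51.8. At r = 0.5, b = 0.71, so a 1-SE imbalance shifts the estimate by -0.29 × 21.1 = about -6 m. The shift is nil at r = 51.8/73.6 = 0.704 and changes sign above that. ANCOVA removes this linear part.

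**5. Power at 12 per arm.** Change score: SD as in step 1, 22 degrees of freedom. ANCOVA: residual SD = SD after × sqrt(1 - r²), 21 degrees of freedom, variance multiplied by 1 + 1/(2n - 4) for estimating the slope. The equal-SD case uses sqrt((51.8² + 73.6²)/2) = 63.6 m at both times.

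| r | Pilot SDs: change → ANCOVA | Equal SDs: change → ANCOVA |
|---|---|---|
| 0.3 | 44% → 48% | 45% → 60% |
| 0.5 | 56% → 56% | 58% → 68% |
| 0.7 | 75% → 72% | 80% → 84% |
| 0.8 | 87% → 86% | 93% → 94% |
| 0.9 | 97.5% → 98.7% | 99.8% → 99.8% |

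Simulation with 20,000 runs agrees (pilot SDs: 55.7% and 56.3% at r = 0.5; 74.6% and 72.5% at r = 0.704). If the SD rises only in the trained arm and controls stay at 51.8 m, simulation gives about 51% → 60% at r = 0.3, 64% → 68% at r = 0.5, and a loss of about 1 point at r = 0.7 to 0.8.

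**The case against.** The strongest reply is that the planned analysis is sound and ANCOVA buys little on the protocol's own figures. The interaction is unbiased under randomisation, keeps its type I error rate and also gives an effect in metres. With the pilot SDs and the lost degree of freedom counted, ANCOVA is level at r = 0.5 and slightly worse from about 0.6 to 0.8. Simply naming the interaction would settle which term decides, with no change of model. All of this stands.

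It also limits what a reader might infer. The familiar variance ratio (1 + r)/2 suggests that ANCOVA always gives clearly more power at no cost. That ratio requires equal SDs before and after, whereas the pilot SDs rise from 51.8 to 73.6 m, and r is nowhere stated. The pilot is a single trained group, however, so the rise may not apply to controls; neither SD scenario can be taken as fact.

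A case for adding sex is weaker still. Both sexes are enrolled, and the arm curl test uses "2-kg dumbbells for women and 4-kg dumbbells for men", but that is a different outcome and each person's load is the same before and after. If sex explains nothing beyond baseline, including it costs about two more points of power.

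The reply does not reach the imbalance point. Naming the interaction leaves the shift in step 4 in place, and at this sample size it is not negligible unless r happens to be near 0.7.

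**Conclusion.** This is a cheap improvement, not an error in the plan. Two things hold: the article does not identify the term that answers the randomised question, and the term that does answer it leaves chance baseline imbalance imperfectly corrected. The size of the second is about 6 m per 1-SE imbalance at r = 0.5, against a hoped-for 58.9 m. The change-score reading rests on two 6MWT occasions, which is inferred.

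On power, the honest statement is a range. In the scenarios computed, ANCOVA gains up to about 15 points and loses at most about 2, depending on the unstated correlation and SDs. A reader might conclude that ANCOVA would make good the power of this small trial; the figures do not support that. At 12 per arm and r = 0.5 it gives 56% with pilot SDs and 68% with equal SDs, both below 80%. The sample-size shortfall is a separate matter.

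**What to change.** For the normally distributed outcomes, replace the mixed ANOVA as the between-group test by an ANCOVA of the week-12 value on group, with that outcome's own baseline value as covariate. Report the adjusted mean difference with its 95% confidence interval. Name the group coefficient for 6MWT as the primary test. Present time effects and within-group contrasts as descriptive only. Sex as a further covariate is optional and, if wanted, should be fixed in advance.

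The cost is a change of wording and one residual degree of freedom, with at most about 2 points of power lost in some scenarios; optional sex adjustment would take one more degree of freedom. No new measurement is needed, since baseline is already assessed before randomisation. The text should not promise a fixed gain in power.

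### For non-normal outcomes, the main outcome not exempted, the fallback names no between-arm test that uses baseline or change

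*Protocol article*

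**What the plan says.** All of this stands in the Analysis section of the protocol article, except where noted.

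- **Gate.** "The normality and homogeneity of data variance will be verified through the Shapiro–Wilk and Levene tests, respectively". The choice of method then depends on whether the variable is normally distributed. The text does not say whether raw scores, changes or residuals are tested.
- **Normal branch.** "the two-way mixed-design analysis of variance (ANOVA) test (a repetition factor and a group factor), followed by Bonferroni post hoc, will be applied". This model contains the group-by-time interaction, which compares change between arms. Bonferroni applies here to the post hoc tests.
- **Fallback.** "the Wilcoxon tests will be used to compare the differences between times and the Mann–Whitney test to compare differences between groups". No change score, baseline covariate or counterpart to the interaction is named.
- **Multiplicity in the fallback.** "In this case, the Bonferroni adjustment will be used", set in advance. The number of comparisons is not given.
- **Level.** "In all tests, the significance level of 5% will be considered". The text does not say whether this is per test or familywise.

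The Sample size section makes the six-minute walk distance the main outcome. Nothing exempts it from the gate.

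**The concern.** The trial asks whether the water group changes more than the control group. The normal branch can answer that through the interaction. The fallback puts two other tests in its place: one between times and one between groups. If the first is run within each arm and the second on week-12 values, neither compares change between the randomized arms.

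Two things are at stake. An outcome could be called improved because the water group reached significance and the control group did not, which can happen when both arms changed equally. Or a real effect could be missed, because the remaining between-arm test ignores baseline and may run at a reduced alpha. Bounded scores (the quality-of-life domains, the sleep index, the sleepiness scale) are the likeliest to enter this branch, but the walk distance can enter it too.

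**Working it through.** **Inputs from the Sample size section.** Pre 566.2 m (SD 51.8), post 625.1 m (SD 73.6), 12 per group before dropout, 5% level, 80% power.

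**Assumptions.** Pre-post correlation r (0.5 or 0.7; not in the article), two-sided tests, the pilot SDs in both arms, normal data unless stated, and two to four Bonferroni comparisons (alpha 0.025 to 0.0125).

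**1. The plan's own figure.**
- Difference: 625.1 − 566.2 = 58.9 m.
- Change SD = √(51.8² + 73.6² − 2r × 51.8 × 73.6). At r = 0.5 this is √4287.7 = 65.5 m; at r = 0.7 it is 52.6 m.
- Standardized paired effect at r = 0.5: 58.9 / 65.5 = 0.90. A two-sided paired t-test then needs n = 12 (power 0.809), and 12 / 0.8 = 15.

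So the stated 12 reproduces as a before-after calculation within one group, given r = 0.5. A t-test on change between arms needs 21 per arm at r = 0.5 and 14 at r = 0.7.

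**2. Separate Wilcoxon tests.** Suppose there is no treatment effect and both arms share the same mean change. If p is the chance that one arm is significant, the chance that only the water group is significant is p(1 − p). Exact signed-rank test, n = 12, change SD 65.5, alpha 0.05, simulated:

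| Common change | p | Water group only |
|---|---|---|
| 0 m | 4.5% | 4% |
| 15 m | 9.6% | 9% |
| 30 m | 26.9% | 20% (0.269 × 0.731 = 0.197) |
| 45 m | 53.9% | 25% |

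At 30 m with Bonferroni, the last column falls to about 15% at 0.025 and 11% at 0.0125. At 45 m it stays at 21–24%.

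**3. Mann–Whitney on week-12 values.** True effect 58.9 m, week-12 SD 73.6, 12 per arm, simulated:

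| Between-arm test | Alpha | r = 0.5 | r = 0.7 |
|---|---|---|---|
| Mann–Whitney, week 12 | 0.05 | 43% | 43% |
| same | 0.025 | 32% | 32% |
| same | 0.0125 | 22% | 22% |
| Mann–Whitney, change | 0.05 | 53% | 71% |
| t-test on change (the interaction) | 0.05 | 56–57% | 75% |
| ANCOVA | 0.05 | 57% | 73–74% |

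With no effect, the week-12 Mann–Whitney test rejects in about 4–5% of trials at 0.05. In a skewed (log-normal) scenario at r = 0.5, the week-12 and change versions have equal power at 0.05, about 72%. At r = 0.7 in the same scenario they have 72% and 86%.

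**4. The gate.** If Shapiro–Wilk is run at 5% on the four group-by-time cells of a truly normal outcome, the chance that at least one rejects is 1 − 0.95⁴ = 18.5% for independent tests. Simulation gives 17–18%.

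**The case against.** **The Mann–Whitney variable is not named.** The text says only that groups are compared. If change scores are meant, the fallback does have a between-arm test of change. The parallel phrasing (times for one test, groups for the other) points the other way, and the reader should not have to guess. What can be said is that the plan does not state that change is compared.

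**A reader might infer that choosing the test after a normality check breaks the 5% level.** The calculations do not support this. Taking Shapiro–Wilk on four cells, then the test on change or a week-12 Mann–Whitney test, the two-stage type I error with no effect was 5.5 / 5.0 / 4.5% at r = 0.5 and 4.7 / 4.4 / 4.0% at r = 0.7, for fallback alpha 0.05 / 0.025 / 0.0125. The between-arm harm is lost power. False claims come from reading the within-arm tests as evidence of effect.

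**A reader might also infer that the Mann–Whitney test is wholly unadjusted, or that Levene's test switches the method.** Neither holds. Bonferroni applies to the fallback, so what is missing is baseline adjustment, and the article attaches no change of method to Levene's test.

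**The common change is hypothetical.** Gains of 30–45 m are half or more of the 58.9 m pilot gain. Controls are told to keep their usual activities, and the walk test is done twice at each assessment to limit learning. This stands: at 0 or 15 m the misleading pattern is much rarer (4% and 9%).

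**Scope.** Only variables that fail the normality check are affected, and part of the advantage over the fallback depends on r. This lowers the weight of the point but does not remove it.

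**Conclusion.** The concern holds in this form: as naturally read, the fallback replaces the group-by-time comparison with tests that do not compare change between arms, and the main outcome can fall into it. The article fixes this branch itself, so it is not a detail left to an analysis plan that is not shown.

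The chance of a misleading within-arm pattern runs from about 4% to 25% at 0.05, depending on an assumed common change of 0 to 45 m and on r = 0.5. That separate within-arm tests do not test the treatment effect does not depend on these assumptions. On normal data with the pilot SDs, the power loss at 0.05 is about 10–14 percentage points at r = 0.5 and 28–32 at r = 0.7. It is larger under Bonferroni, and at 0.05 it vanishes in the one skewed scenario at r = 0.5. The 17–18% misrouting figure holds only if four cells are tested.

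This should be fixed before analysis. It does not invalidate the normal branch.

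**What to change.** State one between-arm analysis per outcome that uses baseline, at one stated alpha and not chosen by a normality pre-test. An example is the baseline-adjusted week-12 difference with its 95% confidence interval, with a permutation, bootstrap or rank version for skewed or bounded scores.

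At the least, if the fallback is kept, say that Mann–Whitney is applied to change scores, at the same alpha as the ANOVA interaction. If Bonferroni is kept anywhere, give the number of comparisons.

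In either case, state that within-arm Wilcoxon and post hoc tests are descriptive and support no claim of efficacy.

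The cost is wording in the analysis section. It needs no new data and places no burden on participants. The article gives the trial status as in data collection, so the change could be settled before the data are analysed.
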